# Evaluating home-based personalised virtual reality physiotherapy rehabilitation compared with usual care in the treatment of pain for people with knee osteoarthritis: protocol for a randomised feasibility study

**DOI:** 10.1136/bmjopen-2025-102994

**Published:** 2025-10-21

**Keywords:** Clinical Trial, Knee, Pain management, Exercise, Feasibility Studies, Rehabilitation medicine

## Abstract

**Introduction:**

Home-based physiotherapy is a current approach to manage knee osteoarthritis (OA). However, adherence to physiotherapy is poor. Non-immersive virtual reality (VR) has shown promise in improving self-efficacy and adherence in other clinical conditions. A non-immersive VR-based home physiotherapy system named Sensor-based Physiotherapy Intervention with Virtual Reality (SPIN-VR) for knee OA has been developed, integrating physiotherapy exercises into engaging games that adjust in difficulty based on real-time performance. This approach aims to enhance exercise adherence by making physiotherapy more enjoyable and personalised. To evaluate the feasibility of this intervention, a randomised controlled trial is being conducted.

**Method and analysis:**

This single-centre, open-label, randomised controlled feasibility trial will evaluate the SPIN-VR system over 12 weeks compared with usual care physiotherapy for knee OA. 50 participants will be randomly assigned to either the SPIN-VR or usual care group, with follow-ups at 12 and 24 weeks post randomisation. The primary outcomes will be a description of feasibility of recruitment, patient willingness to be randomised, the completeness of outcome measures and patient adherence to the intervention. Secondary outcomes include evaluations of muscle strength, endurance, aerobic capacity, exercise technique, central pain processing and self-reported pain mechanisms and moderators. Participants in the intervention arm will be interviewed after 12 weeks to capture their experience in using the VR system.

**Ethics and dissemination:**

This protocol was approved by the Wales Research Ethics Committee 3. Research findings will be disseminated in open-access peer-reviewed journals, to researchers and health professionals through conference presentations, to patients and the public by organising webinars and a seminar.

**Trial registration number:**

NCT06639867.

STRENGTHS AND LIMITATIONS OF THIS STUDYThis study uses a comprehensive set of quantitative outcomes and patient-reported outcomes measures to evaluate feasibility, acceptability and potential mechanisms of effect.The inclusion of qualitative interviews allows further evidence and information about the feasibility of the study and intervention to be gathered.The main limitation of this study is the lack of blinding in the collection of follow-up data. It also lacks a power calculation to examine efficacy.Another limitation is that the standard care arm of the study is not controlled for. Any future studies should compare the intervention against a similar intervention, or a more controlled standard care treatment.

## Introduction

 Osteoarthritis (OA) is a costly major worldwide challenge, impairing function and quality of life. It is one of the leading causes of musculoskeletal pain and disability worldwide,^1^ mainly affecting the knees and hips. The global prevalence of knee OA in 2020 was approximately 7.6% of the global population^2^ and, with an ageing population, the projected rate of years lived with disability is estimated to be 118.5 per 100 000.^3^ Persistent pain is the dominant symptom and can be associated with widespread sensitisation, which may impair neuromuscular control.^4^ OA pain fluctuates, often with intermittent and severe flares from which both symptomatic and functional recovery might be incomplete. Ultimately, pain impairs the differential control of muscles around the painful area, leading to a loss of functional independence and a profound reduction in physical activity, quality of life and mental well-being.^5 6^

Physiotherapy-based exercise is a key non-pharmacological intervention for OA pain management.^7 8^ It offers a safer, low-cost alternative to surgery and long-term medication.^9^,^11^ Exercise reduces pain through multiple mechanisms, including activating endogenous pain inhibition (exercise-induced hypoalgesia),^12^,^14^ improving muscle perfusion^15 16^ and enhancing joint stability during daily activities.^17 18^ However, exercise benefits diminish without continued adherence. A major challenge in translating clinical trial efficacy into real-world outcomes is poor long-term compliance. Prolonged treatment is essential for sustained pain relief and functional improvements.^19^ Patients need skills and motivation to maintain exercises after clinical support ends, as delayed intervention can compromise future treatments like arthroplasty.^20^

Home-based physiotherapy is a promising solution, accommodating individual needs, time constraints and preferences. Studies suggest it can be as effective as clinic-based therapy,^21^,^24^ but adherence remains a concern.^25 26^ Effective home programmes must foster self-efficacy, ensuring exercises are relevant, enjoyable and aligned with patient goals. A Cochrane review found that people are more likely to sustain exercise when it is meaningful and enjoyable,^19^ suggesting that personalised, motivational exercise plans are crucial for long-term success.^19 27 28^

A potential innovative approach to improve physiotherapy is the inclusion of virtual reality (VR) technology. This technology has shown promise in rehabilitating conditions such as stroke and Parkinson’s disease.^29^,^31^ Moreover, a real-time VR feedback game has enabled people with OA to modify their squatting techniques based on targeted feedback.^32 33^ To personalise physiotherapy and allow patients to perform exercises in a controlled and engaging setting, Cardiff University’s Sensor Physiotherapy Intervention (SPIN) Research Group has developed a sensor-based VR physiotherapy intervention following Medical Research Council guidelines.^34^ Wearable and VR technologies can transform home-based physiotherapy for individuals with OA by enhancing adherence, ensuring correct technique and providing instant feedback of pain relief. This VR system integrates physiotherapy principles, movement science, intelligent algorithms and body-worn inertial measurement units (IMUs) to offer real-time and offline feedback on movement quality. It supports the assessment of key biomechanical parameters using data captured from IMUs. Certain parameters, such as joint angle attainment and movement consistency, are used in real time to guide adaptive gameplay. Other parameters, including estimation of squat depth, maximum joint angles, range of motion, movement symmetry and, depending on the sensor configuration, postural sway, are analysed offline to enable a more comprehensive evaluation.

The system is structured around three key components:

Monitoring performance.Exercise goal setting.Exercise progressions.

A built-in algorithm personalises the VR games, adjusting scenarios in real-time based on user progression and exercise quality. Adaptations rely on a composite score that integrates pain severity and movement patterns. When predefined thresholds are reached, task complexity increases, introducing dual-task challenges to maintain patient engagement and motivation throughout their physiotherapy journey. The objective of this feasibility study is to evaluate the practicality of implementing the VR home physiotherapy (SPIN-VR) programme for patient use in a home setting and to assess the feasibility of conducting a larger randomised controlled trial (RCT) to determine the clinical efficacy of SPIN-VR in comparison to usual physiotherapy care provided by the National Health Service (NHS).

## Methods and analysis

### Study design

This is a single-centre, open-label, randomised controlled feasibility trial of a 12-week SPIN-VR programme with a 24-week post-randomisation follow-up. 50 people diagnosed with knee OA who fulfil National Institute for Health and Care Excellence (NICE) and American College of Radiology (ACR) criteria for a knee OA diagnosis^6 35^ will be randomly assigned in equal numbers to either an SPIN-VR programme or to receive usual care physiotherapy.

The study is planned to run from August 2024 to the end of June 2026 when the last patient follow-up is expected.

The study aims to assess the following feasibility outcomes.

### Primary outcome measures

Feasibility of recruitment, measured by enrolling 4 patients per month.Completeness of outcome measures, measured by the number (%) of each questionnaire and mechanistic outcome completed at 12 weeks and 24 weeks post randomisation.Fidelity of healthcare professionals delivering intervention using treatment logs and face-to-face contact, and observation of two assessments and training sessions for setting up patients with knee OA with the intervention.Acceptability of intervention and trial procedures through interviews with patients and staff about expectations and experience of the intervention, and barriers and facilitators to trial participation.Adverse events (AEs) through treatment logs and patient interviews will be used to find issues related to knee symptoms or muscle soreness and falls, and motion sickness, plus any unexpected AEs.Adherence to the intervention by the number of times and date/time of when patients logged in to the VR games and number of physiotherapy follow-up consultations.

### Secondary outcome measures

Evaluate the processes for exercise mechanism of action at improving pain outcomes through a variety of measurements relating to muscle strength and endurance, aerobic capacity, exercise technique, central pain processing, and self-reported pain outcomes and moderators.Assess intervention to treat knee OA using the Outcome Measures in Rheumatology—Osteoarthritis Research Society International (OMERACT-OARSI) core domain set. A variety of patient-reported outcome measures. Pain sensitisation by algometer. Dynamic balance using a step test.

### Participants

The target population is adults with knee OA who fulfil NICE and ACR criteria for knee OA diagnosis^36 37^ and who have been referred to a physiotherapy clinic.

#### Inclusion criteria

Adults aged 45 years or older.Clinical diagnosis of knee OA.Referred for physiotherapy for clinically diagnosed knee OA pain.Activity-related joint pain.Self-reported knee pain on most days for the past 3 months.Average pain severity in the past week of 4 or greater on a 10-point Numeric Rating Scale.Able to understand written and spoken English.Able to provide written informed consent.

#### Exclusion criteria

Where the knee is not identified by the participant as the main source of pain (eg, comorbid painful conditions, widespread pain).

Contraindication to exercise.Pain caused by malignancy, fractures or inflammatory arthritis.Has received surgery for their knee pain in the last 12 months, or had previous knee arthroplasty on the affected knee.Has commenced another new treatment for knee pain, other than the trial interventions, during the preceding 12 weeks.Unable to walk without a walking aid.Unable or unwilling to engage in either active or control intervention.

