### Recruitment

Participants will be identified by a member of the clinical physiotherapy team in outpatient clinics in the University Hospital of Wales in Cardiff. Patients from the waiting list for physiotherapy care, and those already attending musculoskeletal clinics, will be screened. They will be screened for eligibility against the eligibility criteria, and if they are interested, they will be offered a participant information sheet. Contact details will be obtained and passed on to the research team, who will then approach participants to arrange a baseline assessment and informed consent visit. A copy of the consent form is attached in the online supplemental material. Consent to share patient contact details with the research team will be obtained beforehand.

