### Sample size

This feasibility study aims to recruit and randomise 50 participants, a sample size chosen to provide adequate precision in estimating key feasibility parameters, specifically retention and adherence rates, with a 95% confidence intervals of approximately ±10%.^49 50^ As the primary objective is to evaluate feasibility rather than effectiveness, no formal power calculation was performed.^51^ The sample size was pragmatically determined based on an anticipated recruitment rate of approximately four participants per month over a 13-month period, with an estimated 60% of eligible patients expected to consent to participation. This conservative sample size is intended to generate essential data to inform the design and sample size calculations of a future pilot or definitive RCT.

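### The exclusion for unwillingness to engage in an arm overlaps with the primary outcome of willingness to be randomised, and can inflate any consent rate per eligible patient

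*Protocol article*

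**What the plan says.** Five places in the protocol article bear on this point.

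- **Abstract, Method and analysis.** The primary outcomes are described as "feasibility of recruitment, patient willingness to be randomised, the completeness of outcome measures and patient adherence to the intervention". No numerator or denominator is given for willingness.
- **Primary outcome measures.** Willingness to be randomised is not in this list. The recruitment item reads "Feasibility of recruitment, measured by enrolling 4 patients per month", a count per unit of time with no eligible denominator.
- **Exclusion criteria.** The last item is "Unable or unwilling to engage in either active or control intervention".
- **Recruitment.** The clinical team screens patients against the criteria, and then, "if they are interested, they will be offered a participant information sheet". The baseline and consent visit comes later.
- **Sample size.** The target of 50 rests on "an anticipated recruitment rate of approximately four participants per month over a 13-month period". The consent assumption that goes with it is expressed per eligible patient: "an estimated 60% of eligible patients expected to consent to participation".

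The Data analysis section adds that the causes of screening and randomisation failure will be tabulated, and that eligibility and recruitment will be described with 95% CIs.

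**The concern.** Being willing to be randomised means being prepared to accept whichever arm is allocated. An eligibility rule that excludes people who would not accept one of the arms therefore selects on the outcome that the abstract sets out to measure. A patient who says no because they want the VR system, or because they do not, is recorded as ineligible and not as eligible and unwilling.

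The study exists to judge whether a larger trial is feasible and to inform its design. It is open-label and compares a new technology with usual care, so arm preference is a plausible reason for refusal. If such refusals drop out of the denominator, the consent rate handed to the planners of the next trial is too favourable, and they may approach too few patients. The monthly recruitment outcome cannot correct this, because it does not show how many patients had to be approached.

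**Working it through.** **Inputs from the document:** 50 to be randomised; about 4 per month for 13 months; 60% of eligible patients expected to consent (all from Sample size).

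**Input not in the document:** u, the share of refusers who are coded as excluded under the unwillingness criterion. It is an assumption and could lie anywhere from 0 to 1.

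**Step 1: the plan's own figure.** 4 × 13 = 52, which agrees with the target of 50. This figure does not depend on the criterion.

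**Step 2: patients implied by 60%.** 50 / 0.60 = 83.3, so about 84 patients must be eligible and approached. Of the 83.3, 33.3 refuse.

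**Step 3: effect of the criterion.** Let E = 50 / true rate be the number who meet every criterion except willingness. Then

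reported rate = 50 / [50 + (1 − u)(E − 50)].

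If the next trial's planners applied the reported rate to all patients who meet the other criteria, the shortfall in the number approached would be 1 − (true rate / reported rate). For a true rate of 60%:

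| u (assumed) | Refusers removed | Denominator left | Reported rate | Shortfall |
|---|---|---|---|---|
| 0 | 0 | 83.3 | 60.0% | 0% |
| 0.10 | 3.3 | 80.0 | 62.5% | 4% |
| 0.25 | 8.3 | 75.0 | 66.7% | 10% |
| 0.50 | 16.7 | 66.7 | 75.0% | 20% |
| 1 | 33.3 | 50.0 | 100% | 40% |

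**Step 4: how much recoding would hide a lower true rate.**

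- True rate 50%: E = 100, with 50 refusers. A reported 60% needs a denominator of 83.3, so 16.7 refusers are removed and u = 16.7 / 50 = 0.33.
- True rate 40%: E = 125, with 75 refusers. A reported 60% needs 41.7 removed, so u = 41.7 / 75 = 0.56.

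**Step 5: scale against sampling error.** With 84 eligible and a rate of 60%, the 95% half-width is 1.96 × √(0.6 × 0.4 / 84) = 0.105. A shift of 6.7 points (u = 0.25) lies inside that margin and one of 15 points (u = 0.50) lies outside it. The confidence interval does not allow for this bias in either case.

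**Step 6: what is unaffected.** The four-per-month outcome counts enrolled patients only, so it is the same at every u.

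**The case against.** The best case for the plan has five parts.

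1. **No denominator is fixed for willingness.** A reader might infer that the outcome is biased by construction. The document does not support that. The upward bias is firm only for a rate per eligible patient, and it is zero if arm-preference refusers are counted as eligible decliners. This stands as a limit on the claim. It does not remove the conflict between a stated exclusion and a stated primary outcome.
2. **The 60% is a planning assumption.** A reader might take it as a test that the study must pass. No threshold or comparison is attached to it, so this stands. The 60% is nevertheless expressed per eligible patient, which is the denominator that the criterion alters.
3. **Not all refusers are removed.** A reader might infer that everyone who declines disappears from the denominator. Patients who decline because of trial burden are untouched by the criterion. Those who are not interested have already been screened when they say so, and nothing in the text makes them ineligible. Many arm preferences will also emerge only after the patient has read about the arms, and the document does not say that such patients are then recoded.
4. **The word either is ambiguous.** It can mean unwilling to do one of the arms, or unwilling to do both. Under the second reading few arm-preference refusers are excluded. This stands, but it leaves the coding to whoever screens.
5. **Failure reasons will be tabulated.** The excluded patients could be added back from that table. This works only if arm unwillingness is recorded as its own reason, which the text does not state. Detailed log codes may reasonably sit in the full protocol.

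**Conclusion.** The concern holds in a limited form. Read as unwillingness to accept one arm, the exclusion overlaps with the willingness outcome and pushes any consent rate per eligible patient upward. The direction is certain whenever at least one refuser is coded ineligible under the criterion. The size is unknown, because the document gives no basis for u, and the reported rates for a true 60% are illustrations. The shortfall for a future trial also assumes that its planners use the reported rate without adding the excluded patients back.

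The document does not show that the outcome has been biased, and the target of 50 and the monthly recruitment outcome are not affected. The mismatch between the abstract, which names willingness as primary, and the Primary outcome measures list, which omits it, needs correcting under any reading of the exclusion. The change is worth making now, since a refusal reason not logged at screening may not be recoverable later.

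**What to change.** - Define willingness to be randomised as the number randomised divided by the number who meet every criterion except willingness. Inability to engage can stay an eligibility matter; unwillingness should count as a decline.
- Word the exclusion so that it is clear whether it concerns one arm or both.
- Log three separate reasons among eligible decliners: would not accept the active arm, would not accept the control arm, and would not take part at all.
- Report the rate with a 95% CI beside the 60% planning assumption.
- Add the outcome to the Primary outcome measures list so that it agrees with the abstract.

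The cost is a change to the screening-log codes, a few lines of text and, probably, a less favourable reported consent rate. The sample size, the interventions and the patients who are randomised stay the same.

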### Trial assessments

An assessment will be carried out at the baseline and consent visit with a researcher. During the baseline visit, the research team will collect demographic data. Patients will have two in-person follow-up assessments with the Cardiff University (CU) research team, at 12 weeks post randomisation, which will occur at the end of their SPIN-VR programme, and another at 24 weeks post randomisation. A flowchart of the patient pathway is presented in figure 1.

**Figure 1 F1:**
[figure not shown]
Flow diagram of patient study pathway of recruitment and follow-up. CSRI, Client Service Receipt Inventory; IPAQ, International Physical Activity Questionnaire; PHQ9, Patient Health Questionnaire-9; SPIN-VR, Sensor-based Physiotherapy Intervention with Virtual Reality.

The following assessments will be conducted at both baseline and follow-up visits:

Pain sensitisation, conducted using algometer.Dynamic balance, using a validated step test by asking participants to maintain balance on the study leg, while stepping the contralateral leg on and off a 15 cm step as many times as possible in 15 s without any weight transfer to the stepping leg. A higher number of steps indicates a better outcome.Evaluation of exercise mechanisms of action:Muscle strength and endurance: 30 s time sit to stand test. A faster time indicates a better outcome.^38^Aerobic capacity: timed 6 m walk test. A faster time indicates a better outcome.^39^Exercise technique: throughout exercises by evaluating key biomechanical parameters for each exercise and compared with lab-based data collected on healthy subjects, for example, centre of mass motion.Central pain processing: quantitative sensory testing modality of pressure pain detection thresholds local and distant from the index knee.^40^Self-report measures of pain mechanisms and moderators: activity, medication use, psychological well-being.^41^

Participants will be invited to complete a series of patient-reported outcomes measures (PROMs). These are:

Knee Osteoarthritis Outcome Score (pain, symptoms, activities of daily living, function in sport and recreation, and knee-related quality of life). A higher score indicates a better outcome.^42^EQ-5D-5L Questionnaire (overall health status).^43^Client Service Receipt Inventory (healthcare utilisation, medication use, service receipt for arthritis).^44^International Physical Activity Questionnaire^45^ (physical activity levels).Self-Efficacy for Managing Chronic Diseases 6-Item Scale (confidence in managing chronic disease) A higher score indicates a better outcome.^46^Central Aspects of Pain (constructs associated with pain across musculoskeletal conditions).^47^Pain intensity before and after exercise. A lower score indicates a better outcome.A patient acceptability questionnaire on the SPIN-VR intervention.

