#### Qualitative interviews

Following recruitment, patient interviews will be conducted with a sample of 15 participants after the 12-week intervention. The purpose of these interviews is to gather valuable insights and perspectives regarding the study and the intervention. Topics covered will include the participants’ acceptance of the technology, factors influencing their participation in the trial, any unexpected benefits or adverse effects experienced, as well as their experiences with pain and any impact on their overall function and exercise. Interviews will last between 30 and 45 min. The audio files will be transcribed verbatim by a professional transcription company. The data will be analysed using thematic analysis and NVivo software will be used to manage the data analysis.

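### The 30 s sit-to-stand test is scored by a time that cannot vary, and a timed 6 m walk is the only test assigned to aerobic capacity

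*Protocol article*

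**What the plan says.** Under Secondary outcome measures, the protocol article sets out to study how exercise acts on pain through measures of "muscle strength and endurance, aerobic capacity, exercise technique, central pain processing, and self-reported pain outcomes and moderators". The list in Trial assessments, after Figure 1, then gives a test, and for most tests a direction of benefit, for each domain:

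- Muscle strength and endurance: "30 s time sit to stand test. A faster time indicates a better outcome".
- "Aerobic capacity: timed 6 m walk test. A faster time indicates a better outcome".
- Dynamic balance, a step test: stepping "as many times as possible in 15 s without any weight transfer to the stepping leg", with the rule "A higher number of steps indicates a better outcome".

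No other test in the list is assigned to aerobic capacity. Nothing elsewhere in the article gives a repetition count for the sit-to-stand test or describes a longer walk.

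The Data analysis section plans analyses of change from baseline in the outcome assessments, with two-sided tests at 0.05, and estimates of outcome variances for later power calculations.

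**The concern.** There are two separate faults.

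For sit-to-stand, the test's name fixes its duration and the scoring sentence then asks for a shorter duration. The article therefore does not say what the outcome variable is or which direction is good. It could be a count with the wrong scoring sentence, or a time-to-complete test with the wrong name and no stated number of repetitions. The two have opposite directions of benefit.

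For the walk, the scoring fits a fixed distance but the construct does not. A walk of a few seconds shows how fast someone walks; it is too brief to say much about aerobic capacity. As this is the only test under that label, a change in walking speed could be reported as a change in an aerobic mechanism.

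What is at stake is the reading of two mechanism outcomes, and the choice of outcomes and variance estimates passed to a later trial.

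**Working it through.** The article states no figure that depends on these scores, so there is none to reproduce. The check sets the entries side by side and adds simple arithmetic. Repetition times and walking speeds below are assumptions, because the article gives none.

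**1. Sit-to-stand**

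Input: fixed duration T = 30 s (Trial assessments).

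- Elapsed time is 30 s for every participant, so its variance is 0 and no participant can be faster than another.
- Count = T / (seconds per repetition), which does vary:

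| Assumed seconds per repetition | Elapsed time (s) | Stands in 30 s |
|---|---|---|
| 1.5 | 30 | 20 |
| 2 | 30 | 15 |
| 3 | 30 | 10 |
| 5 | 30 | 6 |

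The better performer has the higher count and the same time.

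**2. Comparison within the same list**

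| Test | What is fixed | Stated score | Can the score vary? |
|---|---|---|---|
| Step test | 15 s | Number of steps, higher better | Yes |
| Sit-to-stand | 30 s | Time, faster better | No |
| Walk | 6 m | Time, faster better | Yes |

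The article scores one fixed-duration test by count and the other by time. Only the first works.

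**3. Walk**

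Input: distance 6 m (Trial assessments). Time = distance / speed.

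| Assumed speed (m/s) | Time for 6 m (s) |
|---|---|
| 0.5 | 12.0 |
| 0.8 | 7.5 |
| 1.0 | 6.0 |
| 1.2 | 5.0 |
| 1.5 | 4.0 |
| 2.0 | 3.0 |

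Across this wide range the whole test lasts 3 to 12 s.

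**4. Metres or minutes?**

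The article abbreviates minutes as min elsewhere, for example "Interviews will last between 30 and 45 min" under Qualitative interviews, so the walk reads as 6 metres. A slip for 6 minutes cannot be excluded. In that case duration is fixed, the outcome is distance with more being better, and a faster time is again undefined. The entry therefore needs correction on either reading: the label if metres, the scoring if minutes.

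**5. Effect of a reversed direction**

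If counts were recorded but read as lower is better, each change X would be interpreted as −X. Since Var(−X) = Var(X), and a two-sided test gives the same p-value for X and −X, the variance estimates and tests would be unaffected. Only the reported direction would be wrong.

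**The case against.** The strongest reply is that this is a drafting slip in one interpretive sentence of a condensed article. The test's name and the adjacent step test make it likely that assessors count stands. The case report forms are mentioned in the article but not shown, and each scoring sentence cites a source that is not at hand. The tests are secondary, the sample size rests on the precision of retention and adherence rates, and the completeness outcome asks only whether each measure was completed. On the walk, the article contains no statement that contradicts the label, so the objection is a judgement about construct validity based on assumed speeds, not an internal contradiction.

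Most of this stands, and it limits severity. It does not remove the point. The article does not leave scoring to a fuller document; it states a scoring rule, and for sit-to-stand that rule cannot work. The walk entry needs correction whichever test was meant.

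A reader might infer more than the documents support:

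- That the sit-to-stand data will have zero spread, or that improvements will be reported as worsening. Either follows only if the sentence is applied literally in data capture or interpretation, and nothing shown establishes that.
- That the walk is also mis-scored. For a fixed 6 m, faster is better is a coherent rule and gives a usable variable whose variance can be estimated.
- That both faults corrupt the variance estimates. A reversed sign does not change a variance, and a mislabelled walk still yields a valid variance for walking time.

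**Conclusion.** The point holds as two distinct corrections of moderate importance.

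The sit-to-stand scoring rule is wrong as written. It needs no outside source: a fixed time cannot rank participants, and the same list scores its comparable test as a count. The walk, if it is 6 metres as printed, is scored coherently but mislabelled, which leaves aerobic capacity without a suitable test among those listed. If it is 6 minutes, the scoring is wrong. The 3 to 12 s duration rests on assumed speeds of 2.0 to 0.5 m/s; that so short a walk reflects walking speed and not aerobic capacity is a judgement, but one that does not turn on the exact speed.

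The consequence is confined to the definition and interpretation of two secondary mechanism outcomes, and to the change analyses and variance estimates that use them. The primary feasibility outcomes and the target of 50 participants do not depend on the scoring of either test. The documents do not show that any data have been recorded wrongly.

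**What to change.** 1. **Sit-to-stand.** Define the outcome as the number of full stands completed in 30 s, with a higher number better. If a time-to-complete test is actually run, rename it, state the number of repetitions, and keep a shorter time as better.
2. **Walk.** Name the test actually performed. Either report it as 6 m walking speed, higher better, and drop the aerobic-capacity label, or report it as 6-minute walk distance, higher better.
3. **Consistency.** If the aerobic-capacity label is dropped, amend Secondary outcome measures and the Abstract, which both name that domain.
4. **Data.** Check the case report form and database field (variable, unit, direction) for both tests before the change-from-baseline analyses and variance estimates. The article expects the last follow-up by the end of June 2026; the check is easier while recorded values can still be verified.

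The cost is a wording correction and a data check, with no effect on sample size. The one real downside is that, if only a 6 m walk is done, the study may lose its aerobic-capacity claim.
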